#### Algorithm feasibility

CCQ and UC group: to assess feasibility of the final algorithm, the algorithm was tested on databases of previous studies in the Wilhelmina Hospital Assen (n=38) and the Isala klinieken Zwolle (n=168).

#### Algorithm example

CCQ group: a high score on CCQ total score (>3, i.e. severely impaired) in combination with the highest score on the functional status domain leads to a pulmonary rehabilitation program advice, while a total CCQ score between 1 and 2 in combination with the highest score on the functional status domain leads to the provision of leaflets on healthy movement. A CCQ total score < 1 represents a very low burden of disease or good disease control, so no change in treatment advice is given. The final algorithm is displayed in Figure 2.

**Figure 2 F2:**
[figure not shown]
CCQ based treatment algorithm.

UC group: the advise is taken directly from the treatment steps in the Dutch general practitioners guidelines, a GOLD III score leads to the advise to use both a short acting and a long acting bronchodilator. In case of more than 2 exacerbations per year also the use of inhalation corticosteroids is advised.

### Measurements

#### Baseline visit and last visit

At each visit, the disease should be stable; in case of an exacerbation visits are postponed, there should be at least 6 six weeks between the end of the exacerbation and the visit. The following parameters are gathered at baseline and last visit:

•Patient demographics: age, gender, marital status, educational level, employment status.

•COPD specific information: smoking status, pack years, duration of COPD.

•Previous participation in a formal smoking cessation program, pulmonary rehabilitation or reactivation program.

•Co-morbidities, using the Charlson comorbidity index [29].

•Medication use and exacerbations in the last year. Exacerbations are defined as an increase in or new onset of more than one respiratory symptom (cough, sputum, sputum purulence, wheezing, dyspnea) with a duration of two or more days requiring treatment with an antibiotic and/or systemic steroid [30].

•Spirometry, pre- and postbronchodilator FEV_1_ in liters, FEV_1_ % predicted, FVC %predicted, and inspiratory capacity. The bronchodilator will be administered as salbutamol 4 times 100 microgram per metered dose inhaler with chamber device.

•Body Mass Index

•Functional exercise capacity as measured by the 6 minute walking test [31]. The patients are asked to walk up and down a level 30 meter walkway for 6 minutes. Breaks are allowed if necessary and recorded. Total distance walked is recorded as well as heart rate, blood pressure, Borg dyspnea score and oxygen saturation immediately before and after the test.

•Patient reported outcomes:

•The SGRQ is a 50-question, 76-item, health status scale for COPD patients. The SGRQ has 3 subscales: symptoms, activities and impact. The score ranges from 0 (best) to 100 (worst). The minimal clinically important difference is 4 points [32,33].

•The Clinical COPD Questionnaire is a 10-item health status scale measuring three domains: symptoms, functional status and mental state of COPD patients. Scores range from 0 (best) to 6 (worst). The minimal clinically important difference is 0.4 [34,35]. The CCQ has also been validated on the individual patient level [15].

•The modified Medical Research Council (mMRC) dyspnea scale [36]. This measures dyspnea on a scale of 0 (not breathless except when performing strenuous exercise) till 4 (too breathless to leave the house or breathless when dressing).

•The Hospital Anxiety and Depression Scale, a scale developed to identify anxiety disorders and depression among patients in non-psychiatric hospital clinics but also widely used outside the hospital. It is divided into an Anxiety subscale and a Depression subscale both containing seven items. Each question is answered on a 0 to three scale. A total score above 8 suggests the existence of pathology. A change of 1.5 in each domain score represents a clinically relevant change [37].

### During each follow-up visit

The following is collected during each follow-up visit: spirometry, pulmonary medication use, generic questionnaire about treatment offered and received, unscheduled visits to the GP or hospital because of pulmonary problems and patient reported outcomes: CCQ, SGRQ, mMRC, EuroQOL-5D and HADS.

### Advices to health care providers

After each visit the GP receives a treatment advice. Depending on the group to which the patient is randomized this is based either on the CCQ (CCQ group) or on the Dutch National guidelines (UC group). In order to check for compliance the GP is asked to report what treatment (pharmacological and non-pharmacological) was offered to the patient. If the GP deviates from this advice he or she is asked to the provide the reason for deviating.

### Outcomes

#### Primary outcomes

The primary outcome is change in SGRQ over time. Because the intervention is guided by the CCQ, a different health status instrument, the SGRQ, is used as primary outcome measure. Treatment of COPD patients in primary care is focused on improvement of health status and reduction of exacerbations. In this perspective it is a logical choice to use a health status questionnaire as an outcome measure.

#### Secondary outcomes

One of the secondary outcomes is the exacerbation frequency as indicated by medication use. This is one of the classical COPD outcomes, and exacerbations have a large impact on patients’ lives.

Other secondary outcome parameters are changes in CCQ score, 6 minute walking distance test, HADS, mMRC, lung function, and differences between the two groups in hospital admissions and mortality.

#### Economical outcome variables

Health care utilization and other direct medical costs are recorded. Data include medication use and all visits to the general practice, hospital, and other health care professionals involved in the management of COPD.

#### Sample size calculation

Sample size calculations are based on difference in change in health status between both groups. Because the intervention is guided by the CCQ, an alternative health status scale, the SGRQ, is used for the power-calculation. Based on 80% power to detect the minimal clinically important difference (4 points on the SGRQ) between the two groups, a sample size of 150 persons per group is needed. The standard deviation of the SGRQ total score in different samples is approximately10-17 (12 used in calculation) [38-42]. The alpha level was set at 0.05.

Taking dropouts into consideration, a sample size of 165 patients / group = 330 patients in total is aimed for.

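### The sample size is set for a difference in SGRQ change but uses an SD described as that of the total score, so the 80% power claim is unsupported as derived, with the direction of error unknown

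*Protocol article*

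**What the plan says.** All the inputs stand in the Sample size calculation section of the protocol article.

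- Quantity powered: "Sample size calculations are based on difference in change in health status between both groups".
- Target: "Based on 80% power to detect the minimal clinically important difference (4 points on the SGRQ) between the two groups".
- Type I error: "The alpha level was set at 0.05". Whether the test is one- or two-sided is not said.
- SD: "The standard deviation of the SGRQ total score in different samples is approximately10-17 (12 used in calculation").
- Result: "a sample size of 150 persons per group is needed".
- Allowance for loss, added afterwards: "Taking dropouts into consideration, a sample size of 165 patients / group = 330 patients in total is aimed for".

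The Primary outcomes section makes change in SGRQ the primary outcome. The Statistical analysis section compares that change between groups with a t-test, and with a linear regression adjusted for educational level, age, gender, current smoking and FEV1. Baseline SGRQ is not among the listed covariates.

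**The concern.** The SD that governs a t-test on change is the SD of change. The section names a different quantity, the SD of the total score in various samples. The link between the two is the correlation between a patient's baseline and two-year scores, which is not given. No reason is given for choosing 12 from a range of 10 to 17, and 150 per group leaves little margin if the SD of the analysed change is larger.

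The 80% figure for a 4-point difference is the only justification offered for the size of the trial. A null result would naturally be read against it, as evidence that a benefit of 4 points is unlikely. That reading is only as good as the SD behind it.

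**Working it through.** **Inputs.** From the Sample size calculation section: difference 4, SD 12 (range 10 to 17), alpha 0.05, power 80%, 150 per group. Assumed because not stated: a two-sided test, and a baseline to 24-month correlation r between 0.3 and 0.7. Power values are from the noncentral t distribution with 150 per group.

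**Step 1. The plan's own figure.** n per group = 2 × (z for alpha/2 + z for power)² × SD² / difference² = 2 × (1.960 + 0.8416)² × 144 / 16 = 141.3, so 142. The exact t calculation gives 142.2, so 143. The stated figure is 150, about 5% higher. Power with 150 at SD 12 is 82%. Other readings do not give 150 either: one-sided at 80% power needs 112, one-sided at 90% needs 155, and two-sided at 85% needs 162. Loss to follow-up does not explain the gap, because it is added separately (150 to 165). An SD of about 12.3 printed as 12, or rounding up, would explain it.

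**Step 2. From score SD to SD of change.** With equal variances at both visits, SD of change = score SD × √(2(1 − r)). The two are equal only when 2(1 − r) = 1, that is r = 0.5.

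| Score SD | r | SD of change | Power, 150 per group |
|---|---|---|---|
| 12 | 0.3 | 14.2 | 68% |
| 12 | 0.5 | 12.0 | 82% |
| 12 | 0.7 | 9.3 | 96% |
| 17 | 0.3 | 20.1 | 40% |
| 17 | 0.5 | 17.0 | 53% |
| 17 | 0.7 | 13.2 | 75% |

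**Step 3. The quoted range used directly as the SD of change,** which is how the calculation treats 12.

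| SD of change | Power, 150 per group |
|---|---|
| 10 | 93% |
| 12 | 82% |
| 13.5 (midpoint) | 73% |
| 15 | 63% |
| 17 | 53% |

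Power reaches 80% only up to an SD of about 12.3. On this reading (17 − 12.3)/7, about two thirds of the range, falls short.

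**Step 4. How Step 3 depends on r if 10 to 17 are score SDs.** An SD of change of 12.3 corresponds to a score SD of 12.3/√(2(1 − r)). At r = 0.7 this is 12.3/0.775 = 15.9, so only score SDs above about 16 fall short, some 15% of the range. More than half the range falls short only when r is below about 0.58. From r of about 0.74 upwards, none of it does.

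**The case against.** The best defence has four parts.

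*The 150 is safe at the stated SD.* This stands. A reader might infer from the failure to reproduce 150 that the trial is too small. The figures show the opposite: at SD 12 the plan exceeds its target by about 2 points. The mismatch is one of accuracy in the text, not a shortfall.

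*The wording may be loose.* The section opens by speaking of change, and the phrase about the total score may serve only to separate it from the three subscales. The SDs come from cited sources that are not at hand. So the text does not prove that score SDs were used. It is, however, what the text says, and nothing in the article identifies 12 as an SD of change.

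*If score SDs were used, the plan may be conservative.* This also stands. A reader might infer that power fails over most of the protocol's own SD range. That holds only if 10 to 17 is taken directly as the SD of change. If they are score SDs, it depends on r, and at r = 0.7 the plan is adequate over most of the range. The two criticisms cannot both be pressed without that condition.

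*The midpoint has no special standing.* True: 10 to 17 is a spread over samples, not a distribution. The midpoint is used above only for illustration. What remains is that 12 lies towards the low end of the range and no reason is given for it.

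A table of power by SD could be left to a fuller document. Naming the quantity whose SD was entered could not, since the article states that input and describes it as something else.

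**Conclusion.** The point holds as one about the derivation of the power claim. The section sets the sample size for a difference in change and enters an SD described as that of scores, with neither an SD of change nor a correlation to connect them. The 80% is therefore not supported as derived, and the direction of the error is unknown: a score SD of 12 gives 68% power at r = 0.3 and 96% at r = 0.7. Separately, the number said to be needed should be 142 to 143, not 150, a small and conservative discrepancy.

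The documents do not establish that the trial is underpowered. They show only that power could be well below or well above 80% on the information given, and that there is little margin if the SD of change exceeds about 12.3. These results assume a two-sided test, equal variances at the two visits, and values of r that the article does not supply.

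**What to change.** Keep N at 165 per group and restate the section:

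1. Give the assumed SD of 24-month change, or the score SD together with the correlation, and the reason for the value chosen.
2. State the sidedness of the 0.05 level.
3. If 12 is kept as the SD of change and the test is two-sided, say that 143 per group are needed for 80% power and that 150 give about 82%.
4. Show power at 150 per group across the quoted range, for example 93%, 82%, 73% and 53% at SDs of change of 10, 12, 13.5 and 17.
5. Say that a null result will be interpreted by whether the confidence interval for the difference excludes 4 points, not by the planned power.

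These are changes of text only. The cost is that the stated power looks less favourable over part of the range.

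A baseline-adjusted residual SD, score SD × √(1 − r²), would help, but should be quoted only if baseline SGRQ is added to the primary regression model. It is not a listed covariate now, so this would change the analysis and not just the wording. The data are already collected at baseline. For scale, at a score SD of 17 and r = 0.7 the residual SD is 17 × √0.51 = 12.1 and power is 81%, against 75% for the unadjusted t-test on change.

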### Statistical analysis

The primary outcome measures is the change in SGRQ over time. The SGRQ results in a total score and 3 subscale scores: symptoms, activities and impact. The SGRQ change in scores over the treatment period of the control group will be compared to that of the experimental group. The scores will be tested for normality. In case of normality the difference will be univariately tested with a student T-test and multivariately with a linear regression model. In case of deviation from normality the variable will be transformed to normality via a Box-Cox transformation and thereafter analyzed via student T-test and linear regression models.The multivariate models will be corrected for the following confounders: educational level, age, gender, current smoking, and FEV_1_. The number of exacerbations will be reported as weighted exacerbations rates (total number of exacerbations divided by the total person-time of follow up per group) [43-45]. Statistical significance of weighted rate ratios will calculated using a Poisson regression model. The secondary research outcomes will be tested in a similar fashion as the primary research question. The primary analyses will be based on the intention-to-treat principle. As secondary analyses, a per protocol analysis will be performed to increase insight in the data.

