### Randomization and blinding strategy

After inclusion into the study the patients will be randomized to the intervention or usual care group using a computerized randomization on individual patient level. The study will be performed in a double-blind fashion, patients and doctors will be blinded as well as the technicians that perform the measurements. A separate researcher will collect the data, and feed them in to a PC for a computerized treatment advice based on pre-defined criteria as per protocol. This advice will be sent to the doctor. Since the doctor will only see the resulting treatment advices, and not the measurement results they are based on, and since the treatment advices are compliant with the same national guide lines in both groups, albeit organized in a different fashion, blinding is maintained.

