In the current study we decided to randomize on the patient level and not on the GP cluster level. This decision was made after careful evaluation of advantages and disadvantages of randomization on the individual and the cluster level. In this evaluation the following factors played a pivotal role. A large disadvantage of cluster randomization is the risk of selective inclusion, i.e. the physician is more likely to discover to which treatment group all his or her patients are allocated and this might, unconsciously, play a role in selecting patients for participation in the study. A second large disadvantage is the need for a much larger study population to maintain sufficient power. An additional power calculation assuming 10 COPD patients per practice, and a correlation of SGRQ within primary care practices scores of 0.14 (based on previous unpublished studies in our group), the total number of patients needed to achieve a power of 0.8 is 462. This constitutes an increase in patient number of 40%.

A disadvantage of randomizing at the individual level is the risk of contamination, loss of allocation concealment. This risk is present on both the patient level and on the physician level. On the patient level this is caused by the fact that several patients from one GP practice participate in this study and often patients in one practice know each other. Therefore patients in the control group might know patients that have been randomized into the intervention group and via that route receive information from the intervention group which they then might decide to use for themselves. However, we do not consider this to be a large risk in our study because the experimental treatment does not differ markedly from the usual care treatment, the same treatment elements are used albeit differently organized. In other words none of the patients will receive completely new and unexpected advices and therefore we expect them to conform to the recommendations given by their physicians.

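### The primary analysis has no practice term although the protocol cites a within-practice SGRQ correlation of 0.14; the analysis is valid but gives up a little precision

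*Protocol article*

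**What the plan says.** The Randomization and blinding strategy section allocates patients by "computerized randomization on individual patient level". It neither describes nor rules out stratification by practice.

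Under Statistical analysis, "The primary outcome measures is the change in SGRQ over time", and "the difference will be univariately tested with a student T-test and multivariately with a linear regression model". The regression adjusts for five patient-level variables: educational level, age, gender, current smoking and FEV1. Practice or GP appears in neither analysis. Secondary outcomes are handled in the same way, and exacerbation rates are compared by Poisson regression, also without a practice term.

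The Discussion, in arguing against cluster randomisation, assumes 10 patients per practice and "a correlation of SGRQ within primary care practices scores of 0.14 (based on previous unpublished studies in our group". It also states that a practice will contribute several patients.

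**The concern.** The protocol treats practice as a source of outcome variation when it chooses the unit of randomisation, then leaves practice out of the analysis. If outcomes within a practice are correlated, part of the patient-to-patient variance lies between practices. Without a practice term that part stays in the error variance, so the standard error of the treatment effect is larger than it needs to be. At stake are a few points of power for the primary comparison and, in the same direction, for the secondary ones. The Discussion links guideline adherence to practice organisation, and notes that practice nurses often carry out the advice. Practice could therefore plausibly affect the change in SGRQ and not only its level.

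**Working it through.** **Inputs**
- Difference and power: "Based on 80% power to detect the minimal clinically important difference (4 points on the SGRQ) between the two groups" (Sample size calculation).
- "The alpha level was set at 0.05". Sidedness is not given; two-sided is assumed.
- "a sample size of 150 persons per group is needed" (same section).
- "The standard deviation of the SGRQ total score in different samples is approximately10-17 (12 used in calculation". This is the SD of the score; the calculation applies it to the difference in change.
- ICC 0.14 and m = 10 patients per practice (Discussion). The 10 belongs to a hypothetical cluster trial and is an assumption here.

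**1. The plan's own figure.** n per group = 2(1.96 + 0.842)² × 12² / 4² ≈ 141.3, so 142 (143 with the exact t distribution). The stated 150 is somewhat larger, on the safe side, and 150 × 1.10 = 165 gives the recruitment target. With 150 per group the standard error is 12 × √(2/150) = 1.386, the standardised difference is 4 / 1.386 = 2.89, and power from the noncentral t is 82.1%.

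**2. Random practice intercept, simple individual randomisation.** About (m−1)/m of the information on the treatment effect lies within practices, where the relative variance is 1−ICC. About 1/m lies between practices, where it is 1+(m−1)ICC. The variance of the treatment effect relative to the analysis without practice is

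R = 1 / [ ((m−1)/m)/(1−ICC) + (1/m)/(1+(m−1)ICC) ].

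At ICC 0.14 and m = 10: R = 1 / (0.9/0.86 + 0.1/2.26) = 1 / (1.0465 + 0.0442) = 0.917, a cut of 8.3%.

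**3. Power for 4 points, SD 12, 150 per arm** (noncentral t, SD multiplied by √R)

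| ICC of the change in SGRQ | R | Power |
|---|---|---|
| no practice term | 1 | 82.1% |
| 0 | 1.000 | 82.1% |
| 0.06 | 0.978 | 82.9% |
| 0.10 | 0.950 | 84.0% |
| 0.14 | 0.917 | 85.2% |

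The 0.06 row is there because the Discussion's total of 462 for a cluster design implies it on a base of 300: 462/300 = 1.54 = 1 + 9 × 0.06. On a base of 330, which matches the stated 40% increase, the implied ICC is (1.40 − 1)/9 = 0.044 and power is 82.5%. With the stated 0.14, 300 × (1 + 9 × 0.14) would be 678. That mismatch is a separate matter, but it means that 0.14 is not a firm figure.

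**4. Arms balanced within every practice.** Then R = 1 − ICC = 0.86, a cut of 14%, and power is 87.3%.

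**5. Other settings.** At SD 17, the top of the protocol's range, power at ICC 0.14 is 52.8% without a practice term, 56.4% with a random intercept under simple randomisation, and 59.1% with balance. With 4 patients per practice at SD 12 and ICC 0.14, R = 0.954 and power is 83.8%. Fixed practice effects under simple randomisation give R = (1−ICC)/0.9 with m = 10. This exceeds 1 when the ICC is below 0.10, so fixed effects can lose precision.

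**6. Simulation check** (30 practices of 10, ICC 0.14, SD 12, 10,000 runs per scenario; the practice-adjusted analysis used the true ICC)

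| Randomisation | Analysis | Type I error | Power |
|---|---|---|---|
| simple | t-test | 4.9% | 82.3% |
| simple | practice-adjusted | 5.0% | 85.0% |
| balanced within practice | t-test | 3.5% | 84.5% |
| balanced within practice | practice-adjusted | 5.1% | 87.8% |

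**The case against.** The strongest reply is that nothing in the plan is wrong. Allocation is by individual patient, so the t-test and regression hold their level without a practice term, and on the plan's own inputs power exceeds the 80% target. That stands in full.

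The cited 0.14 describes SGRQ scores, while the endpoint is the change in SGRQ. Stable differences in level between practices cancel in a change score, so the relevant ICC may be smaller and the gain may vanish. This also stands, and is why a range is shown. The number of patients per practice in the trial itself is not given either, and fewer per practice means a smaller gain.

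Three stronger readings are tempting, and the document supports none of them.
- A reader might infer that ignoring clustering biases the comparison or inflates the type I error, as it would in a cluster trial. Under simple individual randomisation it does neither.
- A reader might credit the practice term with the full 14% cut in variance and 87% power. That requires arms balanced within practice, which the article does not state.
- A reader might count chance imbalance of arms across practices as a second harm. It is ordinary random error, already covered by the unadjusted standard error.

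Finally, an article may leave blocking details to the full protocol, so their absence is no fault. The tests and the adjustment variables, however, are fixed in the text, and the point rests on those.

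**Conclusion.** The point holds as a minor, nearly free improvement and not as an error. The planned analysis is valid but leaves out a variable that the protocol itself regards as related to the outcome. Under simple randomisation, with SD 12, 150 per arm and 10 per practice, a random practice intercept is worth between 0 and about 3 points of power over an ICC of the change from 0 to 0.14. At 0.14, the 8.3% cut in variance corresponds to about 25 of 300 patients (0.083 × 300). If arms are in fact balanced within practice, the gain at 0.14 is about 5 points over the nominal 82%. In that case the t-test without practice is conservative, because practice differences cancel from the treatment estimate but remain in its estimated standard error. Adding baseline SGRQ to the model, which the stated list does not include, might capture some of the same variance, so the two gains should not be added together.

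**What to change.** Add a random intercept for practice to the primary linear model, alongside the stated covariates, and name that model as the primary test in place of the unadjusted t-test. Use the same term in the secondary models, including a practice random intercept in the Poisson model for exacerbations. A random intercept is preferable to fixed practice effects, which can lose precision when the ICC is small.

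State in the analysis plan whether the computerised randomisation was blocked by practice. If it was, the practice term is needed for a test at the nominal level and is no longer just an option.

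The cost is one model term. Recruitment runs through the GP, so practice is known for every patient, and neither recruitment nor the measurements change. The decision should be recorded before outcome data by arm are seen.

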## Discussion

The objective of the MARCH study is to study whether a treatment algorithm that is based on health status as measured by CCQ improves health status as measured by SGRQ after two years of use compared to care based on FEV_1_ levels as per regular (GOLD) guidelines.

This study is based on the assumption that treatment based on problems that matter to patients (as reflected in a health status measurement) will have more positive effect on their life than treatment that is based on a single measurement that has little relation with their problems (FEV_1_).

The selection of an appropriate primary outcome measure for the current study was an important issue during the design process. The traditional primary outcome measure in COPD research is lung function, usually represented by the FEV_1_. The US Food and Drug Administration (FDA) and the European Medicines Association (EMA) still routinely require this in pharmaceutical trials. However, FEV_1_ has been found to have a very poor correlation with markers of COPD that seem to matter most to patients, such as exercise tolerance, symptoms and also health status [46,47]. Therefore, currently most researchers regard changes in patient centered outcomes such as health status, symptoms, exacerbations and functional status more important than changes in lung function [47]. Patient centered outcomes better reflect the complexity and the impact of the disease, and several aspects of health status predict clinically meaningful outcomes in COPD [48,49]. For instance, functional status as measured in health status questionnaires has been shown to predict exacerbations [50,51], hospital admissions [50-54] and mortality [55,56]. In most large scale COPD studies, health status is measured and demonstrated to improve after successful interventions, but it is seldom used as primary outcome. The situation is different in pulmonary rehabilitation studies where health status has been used as one of the primary endpoints [57].

Using health status as primary outcome measure in a study where the treatment in one arm is organized according to health status carries the risk of direct influence on the outcome. In order to reduce this potential methodological problem, a different health status questionnaire (SGRQ) is used in our study instead of the questionnaire that is used to guide the treatment (CCQ).

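### The SGRQ change analysis adjusts for five covariates but not for baseline SGRQ, which gives up precision at no saving

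*Protocol article*

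**What the plan says.** The Statistical analysis section of the protocol article defines the primary contrast on change: "The SGRQ change in scores over the treatment period of the control group will be compared to that of the experimental group". It gives two analyses of that contrast: "In case of normality the difference will be univariately tested with a student T-test and multivariately with a linear regression model". If the scores are not normal, both are to be run after a Box-Cox transformation. The covariates of the regression are then spelled out: "The multivariate models will be corrected for the following confounders: educational level, age, gender, current smoking, and FEV_1".

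Baseline SGRQ is not in that list, and no other section adds it. It will be available, because SGRQ is among the patient-reported outcomes under the heading Baseline visit and last visit: "The following parameters are gathered at baseline and last visit". The Randomization and blinding strategy section describes individual computerised randomisation and mentions no balancing on SGRQ. The remaining secondary outcomes are to be tested in the same way as the primary one.

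**The concern.** Baseline SGRQ would be expected to predict two-year SGRQ, and change from baseline, better than the five listed variables do. Analysing change does not adjust for it. Subtracting the baseline fixes its slope at 1, whereas the slope in the data will be nearer to r when the variances at the two times are similar. The difference has two effects. The estimate is noisier than it need be. And if one arm happens to start with worse (higher) SGRQ scores, regression to the mean makes that arm appear to improve more.

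The listed FEV1 is unlikely to fill the gap, because the article's own rationale is that it tracks health status badly: "FEV_1_ has been found to have a very poor correlation with markers of COPD that seem to matter most to patients".

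At stake are the precision of the primary result and its robustness to a chance imbalance on the outcome itself. Because the covariate list is explicit, this is a stated choice and not a detail left open for a fuller plan.

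**Working it through.** **Inputs from the article (Sample size calculation).** Difference 4 points and power 80%: "Based on 80% power to detect the minimal clinically important difference (4 points on the SGRQ) between the two groups". Significance level: "The alpha level was set at 0.05", taken here as two-sided. Size: "a sample size of 150 persons per group is needed", raised to 165 for dropout. SD 12, from a range of 10 to 17, described as the SD of the SGRQ total score although the quantity powered is the difference in change.

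**Assumed input.** r, the correlation between baseline and two-year SGRQ, is not given. I use 0.6 to 0.8, with 0.4 as a low value, and assume equal variances at the two times.

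**The plan's own figure.** n per arm = 2 × (1.96 + 0.842)² × 12² / 4² = 141.3, so 142 (143 with the exact t distribution). The stated 150 is slightly larger. Power at 150 is Φ(4 / (12 × √(2/150)) − 1.96) = Φ(2.887 − 1.96) = 82.3% (82.1% by exact t). The difference is on the safe side and does not affect this point.

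**Variance ratio.** With score SD σ, the per-patient variance is 2σ²(1 − r) for change and σ²(1 − r²) after baseline adjustment. The ratio of adjusted to change is (1 + r)/2, which is 0.80, 0.85 and 0.90 at r = 0.6, 0.7 and 0.8. Adjustment therefore needs 10 to 20% fewer patients. Put the other way, the change score needs 1/0.90 to 1/0.80, or 11 to 25% more.

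**Power at 150 per arm, 4 points (normal approximation).**

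Reading 1, 12 is the SD of change. Adjusted SD = 12 × √((1 + r)/2).

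| r | Power, change | Power, adjusted | n per arm for 80%, change / adjusted |
|---|---|---|---|
| 0.6 | 82.3% | 89.8% | 142 / 114 |
| 0.7 | 82.3% | 87.9% | 142 / 121 |
| 0.8 | 82.3% | 86.1% | 142 / 128 |

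Reading 2, 12 is the SD of the score, as worded. Change SD = 12 × √(2(1 − r)); adjusted SD = 12 × √(1 − r²).

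| r | Power, change | Power, adjusted | n per arm for 80%, change / adjusted |
|---|---|---|---|
| 0.4 | 75.0% | 88.3% | 170 / 119 |
| 0.6 | 89.8% | 95.0% | 114 / 91 |
| 0.7 | 96.1% | 98.1% | 85 / 73 |
| 0.8 | 99.5% | 99.8% | 57 / 51 |

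The two readings coincide at r = 0.5. All gains are against the unadjusted t-test.

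**Chance imbalance, 165 randomised per arm.** The SE of the baseline difference is SD × √(2/165): 12 × 0.110 = 1.32 points at SD 12, and 17 × 0.110 = 1.87 at SD 17. The change-score estimate moves by (1 − r) times the imbalance. For a one-SE imbalance this runs from 1.32 × 0.2 = 0.26 to 1.87 × 0.4 = 0.75 points, against a target of 4.

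**The case against.** Several points can be made for the plan as written.

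- **Validity.** Under individual randomisation, a t-test on change is unbiased and holds its error rate. A reader might infer that omitting baseline SGRQ biases the trial. It does not: the shift from imbalance averages to zero over randomisations and is already reflected in the change-score standard error. What remains is lost precision, and error conditional on an imbalance that has occurred. This objection stands.
- **Power.** A reader might infer that the trial is underpowered. If 12 is the SD of change, the t-test reaches 82% and the 80% target is met. If 12 is the SD of the score, the target is missed only when r falls somewhat below 0.5. The article gives no r, so a shortfall is not shown. This also stands.
- **Size of the gain.** Read as worded, the SD of 12 leaves a gain of about 5, 2 and 0.3 percentage points at r = 0.6, 0.7 and 0.8. The planned regression may also absorb some variance through its five covariates, so its own shortfall against a baseline-adjusted model is unknown. Both limits stand.
- **Two analyses.** The t-test and the regression appear side by side, and neither is named as decisive. A reader might infer an inflated type I error. The article does not say that success on either test would count, so no such inflation can be claimed, and ranking the two is commonly left to a statistical analysis plan.

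None of this defends the covariate list itself. It is explicit, it omits the baseline of the outcome, and nothing elsewhere in the article supplies it.

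**Conclusion.** The point holds as one of efficiency, not of validity. A t-test on change, with a regression that omits baseline SGRQ, is a sound but less precise choice. Against the t-test, baseline adjustment is worth 10 to 20% of the sample size at r = 0.6 to 0.8. In power, that is about 4 to 8 percentage points if 12 is the SD of change, and about 5 points down to under 1 if it is the SD of the score. It reaches 13 points (75% to 88%) on the second reading at r = 0.4. A one-SE baseline imbalance moves the change-score estimate by 0.26 to 0.75 points.

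The omission from the list is certain. Its size depends on the assumed r, on equal variances at the two times, and on which quantity has an SD of 12. The amendment should be made, but the trial does not fail without it.

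**What to change.** Add baseline SGRQ total score to the covariates of the linear regression. Name that model as the single primary analysis of SGRQ total, and keep the t-test on change as a sensitivity analysis. With baseline in the model, the treatment estimate is the same whether the outcome is two-year SGRQ or its change, so the primary outcome need not be redefined. For the continuous secondary outcomes, adjust in the same way for the baseline value of the outcome concerned.

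The cost is a sentence or two in the Statistical analysis section, ideally before any unblinded look at outcome data. It needs no new measurements, visits or patients.
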